### Safety stopping rules

To minimize the risks of IORT, safety will be monitored by a Bayesian stopping rule for the rate of adverse events of interest. Previous experience demonstrated that the incidence of 90-day Clavien-Dindo Grade ≥ IIIa is 25% [23]. Safety will be monitored continuously for 20 patients through day 90.

Adverse events (AE) will be monitored continuously for all patients. A Bayesian safety monitoring rule will be used to evaluate the rate of the AE of interest continuously, from the 3rd evaluable patient, and will suspend accrual at any point if there is sufficient evidence of excessive toxicity. Specifically, the Bayesian toxicity monitoring rule will suspend accrual anytime if the posterior probability of AE of interest being larger than 40%, is 70% or higher. We assume a priori that the experimental regimens has an average risk of 25% and there is a 25% chance that the risk will be 40% or higher. Table 3 summarizes the continuous stopping rule for the 20 evaluable patients for each regimen. For example, if 2 patients out of the first 3 evaluable patients experience adverse events of interest, we will stop accrual. Furthermore, to cautiously assess the toxicity profiles of experimental regimens in the event that accrual is relatively “fast” comparing to the safety assessment duration, the accruals of each cohort will be suspended when 6 eligible patients have been accrued to allow the continuous safety evaluations to be done among the first 6 evaluable patients before further accruals. The accrual would resume only if the Bayesian stopping rule utilized is not met. At any time if the stopping criterion is met, accrual to the trial will be temporarily suspended and the principle investigators and study team will review the toxicity data and recommend either modification or termination of the trial.

**Table 3 Tab3:** Stopping rule for safety

Number patients with toxicity of interest	2	3	4	5	6	7	8	9	10
Total number patients treated	3	4–5	6–7	8–9	10–12	13–14	15–16	17–19	20

Table 4 summarizes the operating characteristics based on 5,000 simulations with 20 evaluable patients in terms of how frequent the study would stop based on the stopping rule under different hypothetical toxicity rates, as well as the average sample sizes.

**Table 4 Tab4:** Operating characteristics of the stopping rule for safety

Underlying risk	0.25	0.30	0.35	0.40
% of time study stops	21.6%	32.1%	45%	58.5%
Expected sample size	16.7	15.2	13.4	11.7

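### Under Table 3, two events in the first two evaluable patients already make suspension certain, yet the stopping rule starts at the third; a 2-of-2 entry would cost nothing

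*Protocol article*

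**What the plan says.** All of this stands in the Safety stopping rules section of the protocol article.

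- **Start:** the rule is evaluated "continuously, from the 3rd evaluable patient".
- **Criterion:** it "will suspend accrual anytime if the posterior probability of AE of interest being larger than 40%, is 70% or higher".
- **Prior:** the regimen is assumed to have a risk that "has an average risk of 25% and there is a 25% chance that the risk will be 40% or higher". No distribution family is named.
- **First boundary:** the worked example is "if 2 patients out of the first 3 evaluable patients experience adverse events of interest, we will stop accrual". Table 3 has the same first entry, 2 events in 3 patients, and no entry for one or two patients.
- **Accrual hold:** accrual is also "suspended when 6 eligible patients have been accrued", to let the first six be assessed.
- **Consequence:** crossing a boundary leads to a temporary suspension and a review of the toxicity data, not to automatic termination.
- **Operating characteristics:** Table 4 gives "operating characteristics based on 5,000 simulations with 20 evaluable patients". At true risks of 0.25, 0.30, 0.35 and 0.40 the trial stops in 21.6%, 32.1%, 45% and 58.5% of runs, with expected sample sizes of 16.7, 15.2, 13.4 and 11.7.

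**The concern.** A minimum number of patients before a monitoring rule applies is normally there to prevent a decision on too little data, on the understanding that the next patients could change the picture. Here they cannot. The first boundary is 2 of 3, so once the first two evaluable patients have both had an event, the third can only make it 2 of 3 or 3 of 3, and both cross. The wait adds time but no information that the rule can use.

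The events counted are complications of Clavien-Dindo grade IIIa or higher, up to death (Study endpoints). The scenario is also the worst early one the trial could meet. If the third patient has not yet had IORT when the second event becomes known, the plan as written allows that treatment to go ahead although the suspension is already settled.

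**Working it through.** **Inputs.** From the Safety stopping rules section: Table 3 boundaries, first look at n = 3, maximum 20 evaluable patients, criterion Pr(risk > 0.40) ≥ 0.70, prior mean 0.25 with Pr(risk ≥ 0.40) = 0.25. Assumption: the prior is a beta distribution.

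**1. Reproduce Table 4.** An exact recursion carries the distribution of the event count from n = 1 to 20 and removes paths that reach a Table 3 boundary, looking first at n = 3.

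| True risk | Stops, printed | Stops, exact | Expected n, printed | Expected n, exact |
|---|---|---|---|---|
| 0.25 | 21.6% | 21.9% | 16.7 | 16.61 |
| 0.30 | 32.1% | 32.8% | 15.2 | 15.11 |
| 0.35 | 45% | 45.7% | 13.4 | 13.39 |
| 0.40 | 58.5% | 59.4% | 11.7 | 11.58 |

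The largest gap in stopping probability is 0.9 points. The simulation error there is √(0.594 × 0.406 / 5000) = 0.7 points, so Table 4 agrees with a rule that starts at the third patient.

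**2. Certainty from Table 3 alone.** With x = 2 at n = 2, the count at n = 3 is 2 or 3. The boundary at n = 3 is 2. Suspension therefore follows with probability 1. No prior is needed for this step.

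**3. The posterior criterion at 2 of 2.** With a Beta(a, b) prior, the posterior after x events in n patients is Beta(a + x, b + n − x). Two priors with mean 0.25 were tried:

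- Beta(0.531, 1.592), solved so that Pr(risk ≥ 0.40) is exactly 0.25. It does not reproduce Table 3 at n = 3, 5, 12 and 19, where it requires 3, 4, 7 and 10 events against the printed 2, 3, 6 and 9.
- Beta(0.25, 0.75), for which Pr(risk ≥ 0.40) = 0.267. It reproduces every boundary in Table 3.

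| Data | Pr(risk > 0.40), Beta(0.531, 1.592) | Pr(risk > 0.40), Beta(0.25, 0.75) |
|---|---|---|
| 1 of 1 | 0.614 | 0.755 |
| 2 of 2 | 0.816 | 0.911 |
| 2 of 3 | 0.658 | 0.745 |

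At 2 of 2 the 70% threshold is met under both priors. At 1 of 1 and at 2 of 3 the answer depends on the prior.

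**4. How often this arises.** Pr(2 of 2) = p²: 0.25² = 6.25%, 0.30² = 9.0%, 0.35² = 12.25%, 0.40² = 16.0%.

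**5. Effect of a 2-of-2 entry.** Every path that starts 2 of 2 now stops at n = 3 and would stop at n = 2. The set of stopping paths is the same, so the stopping probabilities stay at 21.9%, 32.8%, 45.7% and 59.4%. One patient is saved on each such path, so expected n falls by p²: 16.61 to 16.55, 15.11 to 15.02, 13.39 to 13.27, and 11.58 to 11.42. The recursion with the added entry gives the same figures.

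**The case against.** The start at the third patient is stated openly, and the text, the worked example and Table 3 agree on it. A reader might infer that it contradicts the word anytime in the criterion. The documents do not support that: the sentence with the criterion spells out a rule whose start has just been fixed, so anytime means from that start onwards. Some minimum is also reasonable. Under the prior that reproduces Table 3, a single event in the first patient would give 0.755 and suspend the trial. This stands, and the point is one of design, not of consistency.

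A reader might also infer that a further patient, or as many as six, is always exposed. That does not follow. It needs 2 of 2 to occur, and it needs the third patient to be untreated when the second event is known. Patients enrol before SBRT, have surgery 2 to 10 weeks after it and are followed to day 90, so the third may already have been treated. Six is the ceiling set by the accrual hold, not an estimate of exposure; the article gives no accrual rate. Adverse events are in any case followed continuously, and the team could act sooner than the rule obliges it to.

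Finally, under the literal 25%/25% beta prior an event-free third patient brings the posterior down to 0.658, below 0.70, so that patient would then matter. This is correct, and it means that the argument must rest on Table 3. Table 3 is what the trial will apply, so the argument holds for the rule as printed.

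What none of this supplies is a reason to wait at 2 of 2 when the printed table leaves only one outcome.

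**Conclusion.** The point holds as a minor design improvement. Under printed Table 3, two events in the first two evaluable patients determine the suspension, and the 70% criterion is met there under both priors tried (0.82 and 0.91). Waiting for the third can only delay the suspension. The situation has a probability of 6.3% at a true risk of 25% and 16% at 40%. The average gain from acting at once is 0.06 to 0.16 patients, with no change in the probability of stopping.

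The certainty argument and the operating characteristics rest only on Table 3. The posterior figures rest also on a beta prior. The number of patients actually spared depends on accrual speed and on when a patient counts as evaluable, and the article gives neither. There is no error in the rule's start or in Table 4.

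**What to change.** - In Table 3, let the entry for 2 events cover 2–3 patients instead of 3.
- Change the start of the rule to the second evaluable patient.
- State that accrual is suspended for the already planned review when the second event is known, without waiting for a third patient to become evaluable.
- Justify the start at two by the Table 3 argument: 2 of 2 makes 2 of 3 certain, and 1 of 1 does not. Do not justify it by the posterior at 1 of 1, which is 0.61 or 0.76 depending on the prior and so falls on either side of the threshold.

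The cost is one phrase and one table cell. The stopping percentages in Table 4 stay as they are. Its expected sample sizes would fall to about 16.6, 15.1, 13.3 and 11.5 (printed value minus p²). No patients are added and no false suspensions are introduced.

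If the team prefers to keep the start at three, one sentence giving the reason would do. If Table 3 is ever recomputed from the literal 25%/25% beta prior, the boundary at n = 3 becomes 3 events. The certainty argument then no longer applies, and a look at n = 2 would have to be evaluated afresh.

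### Under a single Beta prior, the stated prior and 70% posterior threshold do not generate the stopping boundary in Table 3, so Table 4 does not describe the rule as worded

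*Protocol article*

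**What the plan says.** All of this is in the protocol article, Safety stopping rules.

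- **Prior:** an "average risk of 25% and there is a 25% chance that the risk will be 40% or higher". Neither a distribution family nor parameters are given.
- **Criterion:** accrual is suspended if the "posterior probability of AE of interest being larger than 40%, is 70% or higher".
- **Timing:** monitoring is continuous "from the 3rd evaluable patient" up to 20 patients, which gives 18 sample sizes.
- **Boundary:** "Table 3 summarizes the continuous stopping rule for the 20 evaluable patients". The entries (events/patients) are 2/3, 3/4–5, 4/6–7, 5/8–9, 6/10–12, 7/13–14, 8/15–16, 9/17–19 and 10/20.
- **Worked example:** "if 2 patients out of the first 3 evaluable patients experience adverse events of interest, we will stop accrual".
- **Operating characteristics:** Table 4, "based on 5,000 simulations with 20 evaluable patients", reports stopping in 21.6%, 32.1%, 45% and 58.5% of runs at true risks of 0.25, 0.30, 0.35 and 0.40, with expected sample sizes of 16.7, 15.2, 13.4 and 11.7.

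**The concern.** A prior, a posterior threshold and a starting sample size together determine a stopping boundary. The article prints all three and also prints the boundary, so one can be checked against the other. Under the natural reading they do not match, and one of the mismatches is the article's own illustration.

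This is the only formal decision rule in the article. It monitors the same event as the primary endpoint, and the Statistical analysis and sample size section cites it as a reason for choosing 20 patients. If prior and boundary do not belong together, nobody can reproduce the rule from its description, and a reader cannot tell whether Table 4 shows the properties of the rule that was intended.

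**Working it through.** **Assumption.** The prior is a single Beta(a, b), the conjugate choice for a binary event. The article does not say so.

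**Step 1: Table 4 from Table 3.** I took the Table 3 boundary at n = 3 to 20 and computed exact stopping probabilities by binomial recursion, removing at each n the paths that reach the boundary.

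| True risk | Table 4 stops | Exact from Table 3 | Table 4 expected N | Exact expected N |
|---|---|---|---|---|
| 0.25 | 21.6% | 21.9% | 16.7 | 16.6 |
| 0.30 | 32.1% | 32.8% | 15.2 | 15.1 |
| 0.35 | 45% | 45.7% | 13.4 | 13.4 |
| 0.40 | 58.5% | 59.4% | 11.7 | 11.6 |

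The simulation standard error is √(p(1−p)/5000), or 0.6 to 0.7 percentage points. The largest gap, 0.9 points at a risk of 0.40, is about 1.3 standard errors. Table 4 follows from Table 3.

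**Step 2: the stated prior.** Mean 25% requires b = 3a. Solving P(risk > 0.40) = 0.25 for Beta(a, 3a) gives a = 0.531, hence Beta(0.531, 1.592). No other solution was found for a + b between 0.01 and 10.

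**Step 3: Table 3 from the stated prior.** After r events in n patients the posterior is Beta(0.531 + r, 1.592 + n − r). The entries that fall below the threshold are:

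| Table 3 entry | Posterior | P(risk > 0.40) |
|---|---|---|
| 2/3 | Beta(2.531, 2.592) | 0.658 |
| 3/5 | Beta(3.531, 3.592) | 0.690 |
| 6/12 | Beta(6.531, 7.592) | 0.675 |
| 9/19 | Beta(9.531, 11.592) | 0.676 |

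The other 14 sample sizes agree with Table 3; the closest is 7/14, at 0.7006. Under this prior the whole of Table 3 would need a cut-off between about 65.1% and 65.8%, not 70%.

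**Step 4: what the stated prior and 70% threshold imply.** The boundary they generate is 3/3–4, 4/5–7, 5/8–9, 6/10–11, 7/12–14, 8/15–16, 9/17–18 and 10/19–20. By the same recursion:

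| True risk | Stops: Table 3 | Stops: as worded | Expected N: Table 3 | Expected N: as worded |
|---|---|---|---|---|
| 0.25 | 21.9% | 11.9% | 16.6 | 18.4 |
| 0.30 | 32.8% | 21.4% | 15.1 | 17.3 |
| 0.35 | 45.7% | 34.0% | 13.4 | 15.8 |
| 0.40 | 59.4% | 48.7% | 11.6 | 14.0 |

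**Step 5: which priors do give Table 3.** With the mean held at 25% and the threshold at 70%, Table 3 is reproduced in full for a + b from about 0.78 to 1.285, where P(risk > 0.40) is 26.4% to 26.9%. Beta(0.25, 0.75) has a tail of 26.7% and Beta(0.3, 0.9) a tail of 26.5%.

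**Step 6: sensitivity.**
- *Rounding.* If both prior figures are only rounded to 25%, between 2 and 6 entries still disagree, and no Beta prior on the searched grid matched the full table.
- *25% read as the prior median.* Ten entries disagree.
- *Logit-normal prior with the same mean and tail.* Three entries fall short: 2/3 (0.691), 6/12 (0.686) and 9/19 (0.684).

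**The case against.** **The prior family is unstated.** A mean and one tail probability do not determine a distribution. The count of failures is four under a Beta and three under a logit-normal. A two-component Beta mixture, about 0.72 Beta(0.685, 7.118) + 0.28 Beta(2.370, 1.185), has mean and tail both close to 25% and reproduces all 18 entries. This objection stands: a reader might infer that no prior fitting the text can give Table 3, and that is not so. What remains is that the conventional choice fails, and nothing in the article points to a mixture.

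**The operating rule is clear in practice.** The worked example, Table 3 and Table 4 agree, and a trial team would use Table 3. This also stands. A reader might infer that text and table give opposite instructions at 2 of 3, but the text itself says to stop there. The conflict is between the prior and threshold on one side and the example and tables on the other.

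**The prior text misses by little, and on the cautious side.** At mean 25% the tail needs to be about 26.4–26.9% instead of 25%; Beta(0.29, 0.92), with mean 24.0% and tail 25.2%, also reproduces the table. Table 3 suspends earlier than the literal rule would, and suspension is temporary, pending review. This lowers the severity. It does not remove the mismatch, because this small change in the prior moves the stopping probability by 10 points or more.

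**The 2/3 entry could be given too much weight.** The chance of at least 2 events in 3 at a 25% risk is 3 × 0.25² × 0.75 + 0.25³ = 15.6%, and a reader might infer that this one entry supplies 15.6 of the 21.9 points of stopping. It does not, since many of those paths would cross a later boundary. Changing only 2/3 to 3/3 lowers stopping from 21.9% to 15.1%, a net 6.8 points.

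**Conclusion.** The point holds, conditional on a single Beta prior. The printed prior and 70% threshold then fail to generate four of the 18 entries in Table 3, including the worked example. Table 4 describes Table 3 and not the rule as worded: the two differ by 10.0 percentage points of stopping at a risk of 25% (21.9% against 11.9%) and by 10.7 at 40% (59.4% against 48.7%).

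The article does not show which part is in error. Because Tables 3 and 4 support each other, an approximate description of a prior such as Beta(0.25, 0.75) is a plausible source, but that is a conjecture. A conclusion that Table 3 or Table 4 is miscalculated would go beyond the document. Severity: should be fixed.

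**What to change.** State the prior family and the parameters that generated Table 3. Then reconcile the prior sentence, the 70% threshold, the worked example and Tables 3 and 4, in one of two ways:

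1. If Table 3 is the intended boundary, correct the prior sentence. Tables 3 and 4 and the example then stand. Cost: one sentence.
2. If the stated prior and threshold are intended, regenerate Tables 3 and 4 from them and revise the worked example to match. Cost: two tables and one sentence, from a short computation.

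Neither needs new data. Which boundary applies is for the sponsor to decide.

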### Study design

This is a prospective, single institution, single arm safety study to evaluate the safety and feasibility of implementing IORT in patients with non-metastatic PDAC centered in the head or neck of the pancreas who have been treated with neoadjuvant chemotherapy and SBRT and who are undergoing Whipple procedure. All patients will be discussed in our institutional pancreatic multi-disciplinary clinic. Patients with localized PDAC will be considered for enrolling in the study. Patients will be formally enrolled after completion of chemotherapy and just prior to SBRT. This would allow us to assess treatment response with imaging and exclude patients who developed distant disease during chemotherapy. Table 1 shows the protocol calendar and Fig. 1 displays the protocol schema.

**Table 1 Tab1:** Study calendar

Week# (± days)	− 4–0	1 (± 7 days)	2 (± 14 days)	6 (± 28 days)	9 (± 21 days)	10 (± 21 days)	Q3mos (years 1–2) Q6mos (years 3–5)
Interventions/Procedures							
EUS Fiducial placement		X					
CT Simulation		X					
SBRT × 5 days			X				
Surgery					X		
IORT (15 Gy/1 fraction)					X		
Informed Consent	X						
Inclusion/Exclusion Criteria	X						
Demographics	X						
Medical History	X						X
Medications	X						X
Vital Signs and Pulse Oximetry	X						X
Physical exam	X						X
Height	X						
Weight	X						X
KPS	X						X
ECOG status	X						X
Pre-operative evaluation by surgery				X			
Toxicity Assessment^1^						X^^^	X
*Tests*							
Planning CT Abdomen^2^						X	
Radiographic evaluation^3^				X			X

*EUS* Endoscopic ultrasound, *CT* Computed tomography, *SBRT* Stereotactic body radiation therapy, *IORT* Intraoperative radiation therapy, *KPS* Karnofsky Performance Status, *ECOG* Eastern Cooperative Oncology Group, *CTCAE* Common Terminology Criteria for Adverse Events

^1^CTCAE v5.0 and Clavien-Dindo classification

^2^In Radiation Oncology department

^3^Diagnostic CT Abdomen

^^^Inpatient evaluation: post-operative hospitalization

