#### Surgery

Approximately 1–8 weeks after completion of SBRT, patients will have restaging imaging. The decision for surgical exploration will be at the discretion of the surgical oncologist. Surgery may take place anywhere from 2 and 10 weeks after completion of SBRT. Intraoperatively, a photo will be taken to document dissection of the TV.

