#### Rational for radiation dose

A total radiation dose of 109.5 Gy BED_10_ will be delivered, with SBRT in 40 Gy in 5 fractions (BED_10_ = 72 Gy) and IORT in 15 Gy in 1 fraction (BED_10_ = 37.5 Gy). This dose was chosen because BED_10_ > 100 Gy has been associated with excellent local control in both pancreatic cancer and other solid tumors [18–20]. Stereotactic body radiation therapy to 40 Gy in 5 fractions is recommended by the Australasian Gastrointestinal Trials and Trans-Tasman Radiation Oncology Group [17]. Intraoperative radiation therapy to 15 gy in 1 fraction is a commonly used dose for pancreatic cancer with a range of 12.5–20 Gy in 1 fraction [10–12].

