### Statistical analysis and sample size

Descriptive statistics will be utilized to record patient demographic, disease, and treatment characteristics including age, sex, race, disease extent, chemotherapy, radiation therapy, and type of surgery. Time to event outcomes such as OS, LPFS, DMFS, and PFS will be analyzed using Kaplan–Meier method. Our institution’s data and experience suggest that 15% of patients will not be surgically explored due to development of radiographic metastatic disease or too locally extensive disease after SBRT. An additional 15% will require unexpected arterial reconstruction (exclusion criteria). Therefore, 25 patients will be enrolled with the expectation that 20/25 patients will undergo surgical exploration and IORT. A sample size of 20 patients was chosen because this will enable safety evaluation using a closely monitored Bayesian stopping rule and is also recommended by the literature [21, 22]. There will not be any interim data analysis. Data analysis will occur once the study has been completed.

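### The stopping rule is meant to limit IORT risk but only suspends accrual, about 7 weeks before IORT; enrolled, untreated patients are not held during the review

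*Protocol article*

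**What the plan says.** The protocol article, section Safety stopping rules, gives the purpose: "To minimize the risks of IORT, safety will be monitored by a Bayesian stopping rule for the rate of adverse events of interest". On crossing, the rule "will suspend accrual at any point if there is sufficient evidence of excessive toxicity". The section then repeats the action: "At any time if the stopping criterion is met, accrual to the trial will be temporarily suspended". After that, "the principle investigators and study team will review the toxicity data and recommend either modification or termination of the trial". The extra pause at six patients also acts on accrual.

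The section Study design fixes when accrual happens: "Patients will be formally enrolled after completion of chemotherapy and just prior to SBRT". Table 1 places SBRT in week 2, and surgery with IORT in week 9. The section Surgery gives the permitted range: "Surgery may take place anywhere from 2 and 10 weeks after completion of SBRT".

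**The concern.** Suspending accrual protects patients when enrolment and treatment nearly coincide. Here SBRT, restaging and surgical scheduling lie between them. When the boundary is crossed, some patients may already be enrolled and waiting for surgery, and the stated action does not reach them. IORT is a single 15 Gy fraction and cannot be withdrawn once given.

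Followed as written, the rule lets a patient receive study IORT after the trial's own criterion for excessive toxicity has been met and before the study team has decided anything. The monitored event is a complication of Clavien-Dindo grade IIIa or worse, a range that includes death.

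**Working it through.** **1. The rule's own figures.** A Beta(0.25, 0.75) prior has mean 0.25 and Pr(risk > 0.40) = 0.267. With 2 events in 3 patients the posterior is Beta(2.25, 1.75), and Pr(risk > 0.40) = 0.745, which is at least 0.70, so the rule stops. The same prior gives every cell of Table 3. An exact recursion over 20 patients, looking after each one from the third, gives:

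| True risk | Stops, exact | Stops, Table 4 | Expected N, exact | Expected N, Table 4 |
|---|---|---|---|---|
| 0.25 | 21.9% | 21.6% | 16.6 | 16.7 |
| 0.30 | 32.8% | 32.1% | 15.1 | 15.2 |
| 0.35 | 45.7% | 45% | 13.4 | 13.4 |
| 0.40 | 59.4% | 58.5% | 11.6 | 11.7 |

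The differences are what 5,000 simulations would produce. The boundary is sound; the question is what it triggers.

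**2. The lag.** Week 9 − week 2 = 7 weeks nominally. Adding about one week of SBRT to the permitted 2 to 10 weeks gives roughly 3 to 11 weeks from enrolment to IORT.

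**3. Share of enrolled patients reaching IORT.** The section Statistical analysis and sample size says "15% of patients will not be surgically explored due to development of radiographic metastatic disease or too locally extensive disease after SBRT", and expects a further 15% to be lost to arterial reconstruction: 1 − 0.15 − 0.15 = 0.70. The same section expects 20/25 = 0.80, which is used as a sensitivity value.

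**4. Rough ceiling.** In steady state, IORT procedures falling in a review of W days number rate × share × W/30.4.

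- 0.5 per month: 0.5 × 0.70 × 7/30.4 = 0.08 for 1 week; 0.5 × 0.70 × 28/30.4 = 0.32 for 4 weeks.
- 2 per month: 2 × 0.70 × 7/30.4 = 0.32 for 1 week; 2 × 0.70 × 28/30.4 = 1.29 for 4 weeks.

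The lag does not enter this formula. True figures are lower, because the six-patient pause and the cap of 25 enrolled leave few or no patients waiting at many crossings.

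**5. Simulation** (20,000 trials per scenario). Assumed: exponential enrolment at 0.5, 1 or 2 per month; at most 25 enrolled and 20 given IORT; IORT 49 or 63 days after enrolment with probability 0.70; a pause at six enrolled until those given IORT are evaluable; Table 3 boundaries; true risk 0.25 or 0.40. Counted: patients enrolled before the crossing whose IORT falls within the review. Means per stopped trial:

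| Outcome known at | Awaiting IORT at crossing | Treated in 1 week | 2 weeks | 4 weeks |
|---|---|---|---|---|
| Day 90 | 0.32–0.79 | 0.051–0.104 | 0.098–0.200 | 0.193–0.379 |
| Day 14 | 0.43–1.45 | 0.068–0.229 | 0.136–0.439 | 0.263–0.791 |

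Share of all trials with at least one such patient, outcomes counted at day 90:

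| True risk | 1 week | 2 weeks | 4 weeks |
|---|---|---|---|
| 0.25 | 1.1–1.5% | 2.0–2.6% | 3.8–4.2% |
| 0.40 | 3.1–5.0% | 5.7–8.7% | 10.4–13.0% |

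**6. Sensitivity** (12,000 trials per scenario; 1, 2 and 4 weeks). A lag uniform on 3 to 11 weeks gives 0.052–0.101, 0.105–0.208 and 0.201–0.389 at day 90. With 80% reaching IORT, the day-90 figures are 0.053–0.107, 0.112–0.203 and 0.222–0.378, and the day-14 figures rise to at most 0.27, 0.51 and 0.92.

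**The case against.** The strongest reply is that this argues from silence. The article states no hold, but it does not say that IORT continues, and the full protocol may cover the point. The first part is true and limits the claim. However, the article does describe the action on crossing, more than once, and ties it to accrual each time. The problem lies in the stated action, not in a topic left out.

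A second reply is that accrual may mean entry to the treated cohort: Table 3 counts treated patients, and arterial reconstruction is known only at surgery. The section Study design puts enrolment before SBRT, and the six-patient pause itself separates accrued from evaluable patients. Nothing in the article uses accrual to mean entry to IORT.

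A third reply is that a single-institution team would withhold IORT anyway, or move surgery within its permitted window. It might, but a pre-specified rule is there so that this does not depend on judgement on the day.

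The reply on size largely stands. If the true risk is 40% rather than 25%, the excess is 15 points. That is 0.15 × 0.051 to 0.15 × 0.104, or about 0.008 to 0.016 extra events per stopped trial for a 1-week review, and 0.15 × 0.193 to 0.15 × 0.379, or about 0.03 to 0.06, for 4 weeks. A prompt review removes most of the exposure.

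**Conclusion.** The concern holds. The rule's stated immediate action falls on enrolment, nominally 7 weeks before the exposure it is meant to limit, and no text in the article protects enrolled, untreated patients until the review ends. The review can end in modification or termination that covers them, so the gap is confined to the review interval.

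The effect is small: with day-90 counting, 0.05 to 0.10 patients per stopped trial for a 1-week review and 0.19 to 0.38 for 4 weeks. The section says adverse events are monitored continuously, so early complications may be counted well before day 90, which would bring the larger day-14 figures into play. All these counts rest on assumed accrual rates and review lengths. The mismatch itself rests only on the article's text. It is worth correcting because the remedy is cheap and the exposure is irreversible.

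**What to change.** Add to Safety stopping rules: when the stopping criterion is met, study IORT is also suspended for enrolled patients not yet treated until the study team's review is complete; surgery proceeds without IORT as clinically appropriate.

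Tables 3 and 4 do not change. The cost falls on a patient whose surgery comes inside the review. That patient keeps the SBRT dose, 40 × (1 + 8/10) = 72 Gy BED10, instead of 72 + 15 × (1 + 15/10) = 109.5 Gy, and is lost as an evaluable patient. This includes false alarms, since Table 4 shows crossing in 21.6% of trials at the expected 25% risk. At that risk the simulated loss per trial is 0.01 to 0.02 patients for a 1-week review and 0.04 to 0.06 for 4 weeks with day-90 counting, or 0.02 to 0.05 and 0.06 to 0.16 with day-14 counting. A prompt review keeps it small.

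### The safety stopping rule is stated with two denominators, treated and evaluable patients, and with a 90-day outcome they can give different chances of stopping

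*Protocol article*

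**What the plan says.** All of this is in the protocol article, section Safety stopping rules, unless noted.

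- The lower row of Table 3, the denominator, is labelled "Total number patients treated". The upper row is "Number patients with toxicity of interest".
- The sentence introducing the table uses another unit: "Table 3 summarizes the continuous stopping rule for the 20 evaluable patients for each regimen".
- So does the worked example: "if 2 patients out of the first 3 evaluable patients experience adverse events of interest, we will stop accrual".
- Monitoring is to "evaluate the rate of the AE of interest continuously, from the 3rd evaluable patient".
- Table 4 is "based on 5,000 simulations with 20 evaluable patients".
- The endpoint (section Study endpoints) is binary: a Clavien-Dindo grade IIIa or higher complication within 90 days of IORT.
- The section foresees fast accrual. It pauses once, when 6 eligible patients have been accrued, until the first 6 evaluable patients have been assessed. No later pause is stated.

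**The concern.** A patient is treated on the day of IORT, but an event-free outcome is known only 90 days later. When follow-up overlaps, the number treated and the number evaluable differ at many looks, and the same events can meet the Table 3 boundary under one count and miss it under the other. If patients still in follow-up are in the denominator, they count as event-free and the rule tends to stop too rarely. If patients with an event enter at once and event-free patients enter only at day 90, events arrive first and the rule tends to stop too often.

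This is the only safety stopping rule the article states, and acute toxicity is the primary objective. The study team could apply either count and believe that Table 4 describes it.

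**Working it through.** **Inputs from the article.** Table 3 boundary, taken as printed (events/patients): 2/3, 3/4–5, 4/6–7, 5/8–9, 6/10–12, 7/13–14, 8/15–16, 9/17–19, 10/20. Table 4: stopping 21.6, 32.1, 45 and 58.5%, expected sample size 16.7, 15.2, 13.4 and 11.7, at risks 0.25, 0.30, 0.35 and 0.40.

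**Step 1: reproduce Table 4.** Let f(n, x) be the probability of x events in n patients without having stopped. Then f(n, x) = p·f(n−1, x−1) + (1−p)·f(n−1, x). From n = 3, any mass with x at or above the boundary is moved to stopped. The first look alone gives 3(0.25²)(0.75) + 0.25³ = 0.156 at p = 0.25, and 3(0.4²)(0.6) + 0.4³ = 0.352 at p = 0.40. Carried to n = 20:

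| Risk | Stops, exact | Stops, Table 4 | Expected n, exact | Expected n, Table 4 |
|---|---|---|---|---|
| 0.25 | 21.9% | 21.6% | 16.6 | 16.7 |
| 0.30 | 32.8% | 32.1% | 15.1 | 15.2 |
| 0.35 | 45.7% | 45% | 13.4 | 13.4 |
| 0.40 | 59.4% | 58.5% | 11.6 | 11.7 |

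All four percentages agree within 1 point; the Monte Carlo standard error of 5,000 runs is 0.6–0.7 points. Table 4 therefore corresponds to complete outcomes at each look.

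**Step 2: how the counts part.** Take one IORT every 15 days, so the first six fall on days 0 to 75, before any patient reaches day 90.

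- Patients 1 and 3 have events on days 40 and 70. By day 70 five patients are treated, so the treated count reads 2 of 5 (boundary 3) and does not stop. Among the first 3 patients it is 2 of 3, which stops.
- Instead, patients 4 and 6 have events on days 50 and 80. On day 90 patient 1 completes follow-up. Counting event or day 90, there are 3 evaluable patients with 2 events, which stops. In entry order it is 0 of the first 3 and 2 of the first 6 (boundary 4), which does not.

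**Step 3: size under overlap.** The article gives neither accrual rate nor event timing. Assumed: one IORT every 15, 30 or 60 days; event times uniform over 90 days or early (exponential, mean 12 days); and a fully effective pause after the sixth patient until that patient reaches day 90. There were 20,000 runs per cell. Chance of crossing the boundary, 15 / 30 / 60 days:

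| Count | Events | Risk 25% | Risk 40% |
|---|---|---|---|
| All treated | uniform | 7.9 / 14.2 / 19.6% | 38.7 / 48.9 / 56.1% |
| All treated | early | 18.9 / 21.3 / 21.9% | 55.4 / 58.3 / 59.0% |
| Event or day 90 | uniform | 37.5 / 28.5 / 24.3% | 73.9 / 66.3 / 61.6% |
| Event or day 90 | early | 47.9 / 34.4 / 27.5% | 82.0 / 71.2 / 65.1% |
| Day 90 complete, entry order | either | 22.1% throughout | 59.1% throughout |

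With early events of mean 20 days, the treated count gives about 51 / 57 / 59% at a 40% risk, and event-or-day-90 gives about 46 / 33 / 27% at a 25% risk. With one IORT every 91 days there is no overlap and all counts give about 22% and 59%.

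**Step 4: number treated.** With day 90 complete in entry order, the mean number treated at a 40% risk is 13.6 / 13.2 / 12.2, against 11.7 in Table 4. At one IORT every 15 days, the chance of crossing before all 20 are treated is 53.5%, because a known event waits until day 90 to count. If each row is applied to the first n patients by IORT date and triggered as soon as their events reach the boundary, the set of crossing paths is the one in Step 1. The percentages are then those of Step 1 under any overlap, with a mean number treated of about 11.5–13 at a 40% risk.

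**The case against.** The strongest reply is that one row label is loose. Everything else says evaluable, and wording about the first 3 and the first 6 evaluable patients suggests patients taken in order with outcomes complete. On that reading the stopping percentages equal Table 4 at every accrual rate. This stands, and it rules out a tempting stronger conclusion: that neither count delivers Table 4. The over-stopping figures need a particular meaning of evaluable, event or day 90, which the article does not state. Nor does it exclude that meaning. Waiting for day 90 also sits uneasily with a rule that "will suspend accrual anytime if the posterior probability of AE of interest being larger than 40%, is 70% or higher".

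A second reply is that a condensed article may leave the definition of evaluable to the full protocol. That is fair, and its absence alone would be no finding. The finding is that the rule is printed here with two different denominators.

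Third, the departures depend on assumptions. They are small with slow accrual and, for the treated count, with early events, which are plausible for post-operative complications. The pause at 6 also limits overlap where much of the stopping occurs, and it is included above as fully effective.

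Finally, a reader might take a false stop to mean closure, or suppose that the ethics board relied on these percentages. The documents support neither. Meeting the boundary suspends accrual temporarily for review, and the article says only that the board approved the study.

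**Conclusion.** The point holds as an inconsistency in a printed rule, with consequences that depend on conditions the article does not give. Table 4 is not miscalculated: it reproduces from Table 3 when outcomes are complete at each look. Table 3 as labelled does not deliver it when follow-up overlaps and events are spread over the 90 days: stopping at a 40% risk falls from 59.4% to about 39–56% for one IORT every 15 to 60 days, or about 51–59% if events come early. Counting event or day 90 errs the other way: stopping at a 25% risk rises from 21.9% to about 24–38% (uniform) or 27–48% (early). Day 90 complete in entry order keeps the percentages, but it delays action on known events and treats about 12–14 patients on average at a 40% risk rather than 11.7. The direction and size of any error therefore turn on a choice between denominators that the text leaves unsettled. It should be corrected.

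**What to change.** Use one denominator in the text and in Table 3. State that each row applies to the first n patients in order of IORT date, and that the rule triggers as soon as the events among those n reach the listed number. Known events then count at once, patients in follow-up do not dilute the earlier rows, and Table 4's stopping percentages (about 22% at a 25% risk and 59% at 40%) hold under any overlap.

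Recompute the expected-sample-size row of Table 4 with overlapping accrual under a stated accrual assumption. At a 40% risk it is about 11.5–13 for one IORT every 15 to 60 days, and higher with faster accrual.

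The cost is a few words and one simulation run, with a slightly less favourable expected sample size.
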